## Methods

### Study design

Men, 18–50 years of age, scheduled for ACL reconstructive surgery will be randomized to one of two groups. Although most ACL tears occur in women [2], this study will be limited to men due to the gender-related side effects of testosterone. According to our power analysis, we aim to have at least 7 patients in each group after recruiting and screening approximately 70 patients. The dosing is based on a previous study using supraphysiological dose of testosterone for knee replacement surgery [13]. Intramuscular testosterone cypionate will be used because it has been more widely studied and is less expensive than the gel or patch forms of testosterone. Group 1 will receive testosterone administration, one weekly 200 mg dose intramuscularly of testosterone in sesame oil, for 8 continuous weeks beginning 2 weeks prior to surgery and standard-of-care rehabilitation following surgery. Group 2 will follow the same dosing and rehabilitation schedule but receive a saline placebo instead of testosterone. The dose will be given intramuscularly to minimize systemic side effects; however, we expect the total systemic levels of testosterone to increase to an average of 1200 ng/dl. Lean mass, muscle strength, and physical function will be measured 2 weeks prior to surgery, 1 day prior to surgery, and 6, 12, and 24 weeks following surgery. By administering the dose 2 weeks prior to surgery, there will be sufficient time to develop an anabolic state before the catabolic stimulus of surgery. The dose will continue for 8 weeks to try to maintain muscle mass when there is limited movement and endogenous anabolic stimulus. After 6 weeks from the surgery, testosterone will no longer be administered because KOOS function and sports score appear to stabilize after this time [1]. The study will be a double-blinded experiment.

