### Selection and randomization of subjects

Male participants, 18–50 years of age, who present to the orthopedic surgeon with recent knee trauma will be screened for eligibility. Eligible patients will have had rotational trauma to a previously uninjured knee within the preceding 8 months, ACL insufficiency as determined by clinical examination (positive pivot shift and/or positive Lachmann test), and a score of 5 to 9 on the Tegner Activity Scale (TAS) [12] before the injury (scores range from 1 to 10, with a score of 5 indicating participation in recreation sports, and a score of 9 indicating participation in competitive sports on a nonprofessional level).

All eligible participants (see Table 1) will receive information about the trial orally and in writing. After signing a written informed consent, they will be randomly assigned to undergo either standard-of-care structured rehabilitation with testosterone administration or standard-of-care structured rehabilitation with placebo. An investigator not involved in the randomization procedure will prepare sequentially numbered, opaque, sealed envelopes containing the assigned interventions to ensure randomness which will then be provided to the research pharmacist. The study is a double blind study. Only the research pharmacist will know which patient is receiving study drug or placebo. The surgeon, PI, study team, and physical therapist will not know which study arm the patient was randomized. The protocol for rehabilitation will remain the same for all patients.

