#### Physical function tests

At 2 weeks prior to surgery, 1 day prior to surgery, and 6, 12, and 24 weeks after surgery, tests of maximal muscle strength using a Cybex dynamometer [25–27] will be performed on the subject’s unaffected and affected leg. In addition, knee stability and flexibility tests of the affected leg are typically performed during rehabilitation. During later stages of rehabilitation, tests may include the single leg squat, single leg hop, X-hop, triple hop, and timed hop tests [19, 28–31].

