### Statistical data analysis

Descriptive statistics will be performed for participant characteristics as well as baseline testosterone, strength, and body composition. Comparisons across groups will be made for each measurement (t-test) to determine if bias exists between the randomized groups. If bias does exist, these variables will be included as covariates in the primary analysis. The raw data (pre- and post-test) will be plotted to determine if outliers exist. Because the sample size is small if outliers are found, transformations of the data (e.g. log transformation) will be attempted. If this is not feasible, results will be compared using non-parametric analogs to the parametric tests listed below. Intent to treat analyses for specific hypotheses are listed below. In addition, effect sizes will be computed with Cohen’s D to determine the clinical relevance of the results and assist in powering further research. Analyses will be performed using SPSS for all analyses with α = 0.05. If there is any missing data, the analyses can be performed with the SPSS multiple imputation procedure.

Intent to treat will be tested by comparing changes in lean mass and strength using ANCOVA models, with group adjusting for baseline values. KOOS and TAS scores will be analyzed by ANCOVA models. Physical function tests scores on the Lachman and pivot shift tests will be analyzed by χ^2^ test. The changes in gene expression of *Akt1*, *mTOR*, and *FOXO3a* will be compared by ANCOVA models.

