#### Power analysis

Sample size estimates were computed with Nquery (v4) for α = 0.05 and 1-β = 0.80. Preliminary data was taken from a study that provided 12 weeks of oxandrolone/day in 32 healthy 60–87 year old men [24]. Effects sizes between changes in means from baseline to 12 weeks for lean body mass and maximal voluntary strength were used to estimate the changes in mass and strength for Aim 1. The effect size was 2.0 for mass and 2.03 for strength. For similar effects, a minimum of 6 men would be needed for each group. Assuming a 20% attrition rate [1] and similarly very large effect, our sample of 7 per group should be sufficient to see statistically significant effects.

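### At 7 per group the chi-square approximation is not justified for the Lachman and pivot shift results; use an exact test and report these results as secondary laxity findings

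*Protocol article*

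**What the plan says.** Under Statistical data analysis, the protocol article assigns a method to each outcome. Lean mass, strength, KOOS, TAS and gene expression go to ANCOVA. For the two ligament signs it says "Physical function tests scores on the Lachman and pivot shift tests will be analyzed by" a χ² test, at the general α of 0.05. It does not say whether the signs are binary or graded, or whether a continuity correction applies.

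The numbers are small. Study design says "we aim to have at least 7 patients in each group". Power analysis says "Sample size estimates were computed with Nquery (v4) for α = 0.05 and 1-β = 0.80", that "The effect size was 2.0 for mass and 2.03 for strength", and that "a minimum of 6 men would be needed for each group". It then allows for 20% attrition and concludes that "our sample of 7 per group should be sufficient to see statistically significant effects".

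The same two signs serve at entry. Selection and randomization of subjects requires "ACL insufficiency as determined by clinical examination (positive pivot shift and/or positive Lachmann test").

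The statistical section does recognise that the sample is small. Its remedy is a transformation or a non-parametric analog, but that is triggered by outliers and stands in for the parametric tests only.

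**The concern.** The chi-square test takes its p-value from a large-sample distribution. The usual condition for relying on it is an expected count of at least 5 in each cell. With 14 men that condition looks out of reach whatever the data turn out to be, and the plan's small-sample fallback does not extend to sparse tables. At stake is whether a laxity difference is reported as significant when an exact calculation on the same table would not support it.

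There is also a labelling question. The analysis section calls Lachman and pivot shift physical function tests, yet the eligibility section uses them to diagnose ligament insufficiency. A significant result could be read as evidence on the physical-function hypothesis in the Discussion when it describes knee laxity.

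**Working it through.** **Inputs.** From the protocol article: 7 per group (Study design, Power analysis), 20% attrition (Power analysis), α = 0.05. Assumptions, because the article does not give them: one positive/negative result per man, an uncorrected Pearson test, two-sided testing, and a range of positive rates.

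**The plan's own figure.** A two-sample t-test at two-sided α = 0.05 and effect size 2.0 has power 0.791 at n = 5 and 0.876 at n = 6 per group. The stated minimum of 6 therefore reproduces. It concerns lean mass and strength only; no effect size is given for the laxity signs.

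**Expected counts.** Expected count = group size × column total / N. At 7 v 7 this is 7c/14 = c/2. All four cells reach 5 only if both column totals are at least 10, a sum of 20, but N = 14. The smaller column holds at most 7, so its expected count is at most 3.5 in each arm, and at least two cells always fall below 5. After attrition, 7 × 0.8 = 5.6, so 5 to 6 per arm; the ceiling is 3.0 at 6 v 6 and 2.5 at 5 v 5. Graded coding spreads the same men over more cells.

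**Where the tests disagree.** Pearson X² = N(ad − bc)² / (product of the four margins).

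- 0/7 v 4/7: X² = 14 × 28² / (7 × 7 × 4 × 10) = 5.60, p = 0.018. Fisher: 2 × 35/1001 = 0.070.
- 1/7 v 5/7: X² = 14 × 28² / (7 × 7 × 6 × 8) = 4.67, p = 0.031. Fisher: 2 × (7 + 147)/3003 = 0.103.
- By symmetry, 3 v 7 repeats the first pair and 2 v 6 the second.
- At 6 v 6, 0 v 3: X² = 12 × 18² / (6 × 6 × 3 × 9) = 4.00, p = 0.046. Fisher: 2 × 20/220 = 0.182.

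**Type I error given the total number of positives (Pearson, 7 v 7).**

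| Positives of 14 | Error |
|---|---|
| 3 or fewer, 11 or more | 0 |
| 4 or 10 | 7.0% |
| 5 or 9 | 2.1% |
| 6 or 8 | 10.3% |
| 7 | 2.9% |

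The maximum is 18.2% at 6 v 6 (3 or 9 positives) and 16.7% at 5 v 5 (3 or 7 positives).

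**Unconditional type I error.** This weights the conditional errors by the chance of each total. At 7 v 7 and a common rate of 50%, the rejecting arrangements number 2 × 70 + 2 × 42 + 2 × 308 + 100 = 940, out of 2¹⁴ = 16384, which is 5.7%.

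| Per arm | Maximum | Rate 10% | Rate 20% | Rate 30% |
|---|---|---|---|---|
| 7 v 7 | 5.7% | 0.3% | 1.8% | 3.8% |
| 6 v 6 | 6.8% | 1.7% | 5.3% | 6.8% |
| 5 v 5 | 6.2% | 1.0% | 3.8% | 5.8% |

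**After the change.** Fisher's maximum type I error is 1.3% at 7 v 7, 0.6% at 6 v 6 and 2.2% at 5 v 5. Its power at 7 v 7, for assumed rates, is 0.13 (10% v 50%), 0.44 (10% v 70%) and 0.65 (10% v 80%). Pearson gives 0.33, 0.70 and 0.86.

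**The case against.** The strongest reply is that the error is small on average and depends on details that the article leaves open.

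- **Average error.** The unconditional excess is at most 1.8 percentage points, at 6 v 6. At 7 v 7 the test cannot reject with 3 or fewer positives. This stands. A reader might infer that the chi-square test is invalid, with gross inflation of α; the figures do not support that. They show a p-value that can be wrong by a factor of 3 to 4 in particular tables.
- **Version of the test.** The article says only χ². With a continuity correction, 0 v 4 gives p = 0.076 and 1 v 5 gives p = 0.105, close to Fisher. This stands too, and it is a reason to name the version: the text as written permits the uncorrected test.
- **Seven is a minimum.** True, but all four expected counts can reach 5 only from 10 per arm, and then only at an exactly even split.
- **Physical function is analysed elsewhere.** A reader might infer that laxity is the only named analysis of physical function. It is not. Physical function tests lists Cybex strength at five fixed visits, and strength, KOOS and TAS all have an ANCOVA. The Objectives and Study design do list strength apart from physical function, but KOOS and TAS remain.
- **Squat and hop tests.** The article says "During later stages of rehabilitation, tests may include the single leg squat, single leg hop, X-hop, triple hop, and timed hop tests" and names no analysis for them. A reader might infer a comparison limited to men who progressed far enough to be tested. No such comparison is planned, and an article may leave the analysis of these tests to a fuller document.

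**Conclusion.** The point holds in a limited form. The article names a large-sample test for a comparison that cannot meet its expected-count condition at the planned size, and the outlier-based fallback does not cover it. If the coding is binary and the test uncorrected, four of the possible splits at 7 v 7 (0 v 4, 1 v 5, 2 v 6, 3 v 7, and their mirror images) are significant by chi-square and not by Fisher. Conditional type I error reaches 10.3% at 7 v 7 and 18.2% at 6 v 6, against an unconditional maximum of 5.7% to 6.8%. The rate of positive signs at follow-up is not given, so the error that would actually apply is unknown within that range.

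The label is also wrong by the article's own use of the two signs as evidence of ACL insufficiency. Severity is minor: lean mass and strength sized the trial, both are analysed by ANCOVA, and no main conclusion depends on the laxity test.

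**What to change.** In Statistical data analysis, replace the χ² test for Lachman and pivot shift with Fisher's exact test if the signs are recorded as positive or negative, or with an exact ordinal rank test if they are graded, and state which coding applies. Describe both as secondary knee-laxity results, not as physical function. Physical function is then judged on the KOOS, TAS and strength analyses already named, with no new assessment or endpoint.

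The cost is wording only; no extra data or visits are needed. The downside is that the exact test is conservative and has little power here (0.13 at 7 v 7 for an assumed 10% v 50%, 0.06 at 6 v 6). A non-significant result should therefore not be read as showing equal laxity, and the counts per arm should be reported beside the p-value.

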#### Power analysis

Sample size estimates were computed with Nquery (v4) for α = 0.05 and 1-β = 0.80. Preliminary data was taken from a study that provided 12 weeks of oxandrolone/day in 32 healthy 60–87 year old men [24]. Effects sizes between changes in means from baseline to 12 weeks for lean body mass and maximal voluntary strength were used to estimate the changes in mass and strength for Aim 1. The effect size was 2.0 for mass and 2.03 for strength. For similar effects, a minimum of 6 men would be needed for each group. Assuming a 20% attrition rate [1] and similarly very large effect, our sample of 7 per group should be sufficient to see statistically significant effects.

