#### Drug delivery

Either testosterone or placebo will be injected intramuscularly once per week for 8 weeks, starting 2 weeks prior to surgery and ending 5 weeks post-surgery.

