### Limitations

Testosterone therapy is currently a controversial topic but previous studies have shown positive results [8, 41–48]. It may have been ideal to personalize the supraphysiologic doses according to baseline for each participant. However, for ease of administration and future research viability, we attempted to standardize this value. It may be interesting to note variability of the peak testosterone values and results for those participants. Similarly, there is a large age range of participants and studies have shown differences in testosterone level as early as 40 years of age [44, 48–52]. However, additional studies show that the effects in males will still exist with supraphysiologic doses [48, 53, 54] and we expect an effect to be measured independent of age or race.

Recruitment of participants who meet all inclusion criteria will be challenging. Although we are working with multiple orthopedic surgeons, there are a number of challenges in recruiting patients with ACL injury into randomized clinical trials [55]. It will likely be necessary to recruit and screen approximately 70 participants -- 5 times as many potential participants as our power analysis indicates to demonstrate significant differences.

Additionally, while we aim to work with as few physical therapists as possible and are following a standardized protocol, there are differences in the techniques and progression of individual therapists. We intend to monitor progress of individual participants as standardized as possible and to also focus on the 24 week result as the primary outcome time point.

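### Seven per group falls one short of the plan's own minimum after 20% attrition (a small loss), and the effect size behind the power statement comes from the end of treatment, so it does not support the week-24 primary comparison

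*Protocol article*

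**What the plan says.** The Power analysis section gives its basis as "Sample size estimates were computed with Nquery (v4) for α = 0.05 and 1-β = 0.80". The planning data are described thus: "Preliminary data was taken from a study that provided 12 weeks of oxandrolone/day in 32 healthy 60–87 year old men". From that study the section took "Effects sizes between changes in means from baseline to 12 weeks for lean body mass and maximal voluntary strength", and it reports: "The effect size was 2.0 for mass and 2.03 for strength". It then concludes "For similar effects, a minimum of 6 men would be needed for each group" and continues "Assuming a 20% attrition rate [1] and similarly very large effect, our sample of 7 per group should be sufficient". The Study design section repeats the figure of 7, as a floor for each group.

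Two other sections bear on what this power statement covers. Drug delivery describes injections "once per week for 8 weeks, starting 2 weeks prior to surgery and ending 5 weeks post-surgery". Limitations says that the team intends to "also focus on the 24 week result as the primary outcome time point".

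**The concern.** Two things in the power paragraph do not fit the rest of the plan.

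The first is internal. A minimum of 6 completers and 20% attrition do not lead to 7 randomised.

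The second matters more. The planning effect is a change measured when 12 weeks of dosing ended. The trial will be judged at week 24, long after the last injection, and the article gives no effect size for a period off treatment. The only power statement therefore describes a different contrast from the primary one. If the effect at week 24 is smaller than the on-treatment effect, a null result there could be taken as evidence that testosterone does not preserve muscle, when the trial could not have told the difference. The article expects its results and effect sizes to inform larger studies, so such a misreading would carry forward.

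**Working it through.** **Inputs.** From Power analysis: α = 0.05, target power 0.80, d = 2.0 (lean mass) and 2.03 (strength), minimum 6 per group, 20% attrition, 7 per group. From Drug delivery: last injection at week 5 after surgery. From Limitations: primary time point at week 24. From Statistical data analysis: ANCOVA adjusting for baseline. The article does not say whether the test is one- or two-sided; two-sided is assumed.

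**Method.** Two-sample t-test, power from the noncentral t distribution with df = n1 + n2 − 2 and noncentrality d × √(n1·n2/(n1 + n2)). For ANCOVA one further df is removed. Any gain in precision from the baseline covariate is not counted, because the article gives no correlation.

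**Step 1: the plan's minimum.** At d = 2.0, 5 per group gives 79.1% and 6 per group gives 87.6%, so 6 is the smallest number that reaches 80%. The stated minimum reproduces. A one-sided test would already reach 80% with 4 per group, so the stated 6 fits a two-sided calculation.

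**Step 2: attrition.**
- Expected completers: 7 × 0.80 = 5.6 per group, below 6.
- Number needed: 6 / (1 − 0.20) = 7.5, rounded up to 8 per group (8 × 0.80 = 6.4).
- One loss from 7 is 1/7 = 14%, so 7 covers about 14% attrition, not 20%.

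**Step 3: what this costs at the planned effect.**

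| Completers | d = 2.0 | d = 2.0, ANCOVA df | d = 2.03 |
|---|---|---|---|
| 6 + 6 | 0.88 | 0.87 | 0.89 |
| 5.6 + 5.6 | 0.85 | 0.84 | 0.86 |
| 6 + 5 | 0.84 | 0.82 | 0.85 |
| 5 + 5 | 0.79 | 0.77 | 0.80 |
| Average over random 20% loss from 7 + 7 | 0.83 | 0.81 | 0.84 |

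The last row weights each pair of completer counts by its binomial probability (7 men, retention 0.80). The minimum of 6 has slack because it is a rounded-up integer with about 88% power.

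**Step 4: the time point.** The planning effect runs from baseline to 12 weeks in a study that dosed for 12 weeks, so it is measured at the end of dosing. Here, 24 − 5 = 19 weeks separate the last injection from the primary time point. The planning study also differs in drug, in age (60–87 against 18–50) and in population (healthy men against men having surgery).

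**Step 5: how much waning the design can absorb.** The difference detectable with 80% power is 2.02 SD with 5 per group, 1.88 with 5.6, 1.80 with 6 and 1.63 with 7. At 5.6 per group the margin below the planned effect is (2.0 − 1.88)/2.0 = 6%. The article gives no week-24 effect, so the values below are assumptions showing a range:

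| Assumed d at week 24 | Power, 5.6 per group | Power, 7 per group (no loss) |
|---|---|---|
| 1.75 | 74% | 85% |
| 1.5 | 61% | 73% |
| 1.0 | 32% | 41% |
| 0.5 | 12% | 14% |

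**The case against.** A reader might infer from the 5.6 that attrition alone takes the trial below 80% power. It does not. Average power over 20% loss stays at 0.81 to 0.84 for the planned effects, and only an outcome such as 5 + 5 completers falls to about the target or just under it. Moreover, the article attaches the 80% to the minimum of 6. Of 7 it says only that the number should suffice, on condition of a similarly very large effect, and Study design treats 7 as a floor. All of this stands, and it makes the attrition slip a minor correction.

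A reader might also infer that the trial has low power at week 24. The article does not show that. It gives neither a week-24 effect nor a rate of waning, and the figures for d below 2.0 are assumptions. What stands is narrower: the stated basis says nothing about week 24.

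Finally, a reader might conclude that week 6 should become primary. The documents do not compel it. Limitations names week 24 while discussing differences between therapists in technique and progression, and the Objectives concern the outcome of reconstruction, so week 24 is a defensible question. Nor does the oxandrolone figure establish power at week 6, given the different drug, age group and setting. Changing the primary time point of a registered trial would be a substantive amendment.

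The article does concede that its dose may be too small to have a significant influence, but that does not tell the reader that the power figure belongs to another time point. Multiple imputation, which the article allows for missing data, does not restore information lost to dropout.

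**Conclusion.** The point holds in two parts of unequal weight. The attrition allowance is wrong on the plan's own figures: 8 per group, not 7, would preserve the minimum of 6. The consequence is small, with power about 0.83 on average and 0.79 with 5 + 5 completers at d = 2.0.

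The main part is that an effect size from the end of treatment is used to justify a comparison made 19 weeks after treatment ends. Power at the primary time point is therefore unsupported, and the design has little margin: with 5.6 per group, any week-24 effect below 1.88 SD brings power under 80%. How far under depends on waning that the article does not quantify. The figures assume a two-sided test at 0.05 and equal allocation; the averaged figure also assumes independent 20% losses in each group.

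**What to change.** Rewrite the end of the Power analysis section so that it states four things:

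1. With 7 randomised per group and 20% attrition, about 5 to 6 per group are expected to complete.
2. With those numbers, 80% power holds only for a difference of about 1.8 to 2.0 SD (1.88 SD at 5.6 per group).
3. The effect sizes of 2.0 and 2.03 were observed at the end of treatment in the oxandrolone study, whereas the primary time point here is 19 weeks after the last injection.
4. If the week-24 effect is smaller, power falls (for assumed effects at 5.6 per group: 61% at 1.5 SD, 32% at 1.0 SD, 12% at 0.5 SD), and a null result at week 24 would then be inconclusive rather than evidence of no effect.

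The cost is a less favourable stated figure. No extra patients and no change of primary time point are required. Randomising 8 per group would square the attrition arithmetic, but at the planned effect it is not needed to keep average power above 80%.
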